### **Study design**

The first phase of this study will be a large population-based cohort study to identify incident cases of NVAf between January 1st, 2009 and 30th of June 2019; to determine the proportions of NVAf patients who have received a prescription for OACs or no treatment; to examine predictors of OACs prescribing. Given the described study aims and objectives, this study design will allow for a longitudinal analysis of incident NVAf cases and the subsequent timing of OACs prescribing with no comparator groups.

The second phase will be a comparative cohort study that aims to compare the clinical outcomes of NVAf based on their exposure status to anticoagulation therapy. Both patient groups will be identified from phase one and further divided into comparative groups of patients who have been prescribed OACs and patients with no anticoagulation therapy. The comparison will be undertaken after controlling for factors that could influence a patient's exposure to OACs and the outcomes to be explored, more details provided in section M.

Finally, the third phase of this study will be a separate analysis of the treatment group from phase two who have experienced major bleeding events. This study design is suitable for this phase as it will allow for a longitudinal analysis of NVAf patients from the indexed bleeding events and onward to evaluate the clinical outcomes (i.e. stroke, bleeding reoccurrence and mortality) related to OACs resumption or not and the timing of restarting OACs after the bleeding event, it will also allow for post-haemorrhage assessment of stroke and bleeding risk using different risk scores, and the identification of predictors for not resuming anticoagulation therapy.

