**Outcomes:**

The primary outcomes will be the prescription of OACs either VKA or NOACs, product codes for OACs are described in (Appendix 2). Status of anticoagulation therapy will be classified as either OAC prescribed or OAC not prescribed. OAC prescription will be defined as the presence of any OACs prescription during the study period. Treatment patterns for OACs users will be evaluated for (1) continuous exposure to OACs: no treatment change until end of follow-up period, defined starting from the date of first prescription to the intended duration of that prescription, plus the duration of any overlapping and successive prescriptions of the same drug within 30 days after the expected end of a prescription. For VKAs, INR measurements if available will be treated as indicator for VKA exposure and therefore treated in the same way as prescriptions; (2) OACs discontinuation: no OACs prescription after a period of therapy without resumption of OACs; (3) OACs switch: this will include four switching categories: from antiplatelet only to OACs, from VKA to NOAC, from NOACs to VKA, and between NOACs switches. OACs not prescribed will be defined as no prescription record of an OACs at any time after NVAf diagnosis, this will also include patients prescribed lone antiplatelet therapy. Proportions of patients prescribed antiplatelets such as aspirin or other antiplatelets (i.e., clopidogrel, ticagrelor, or prasugrel) within the study period will be described for both OACs exposed and not exposed patients. Products codes of antiplatelet agents can be found in (Appendix 2).

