**Covariates:**

- Patients' demographic information (age, gender, ethnicity, body mass index (BMI), geographic location (rural vs. urban), smoking status, alcohol consumption, Charlson comorbidity index for the severity of comorbidity (Appendix 4), electronic frailty index (eFI), and the index of multiple deprivation (IMD).
- For the sub-group of patients with NVAf and history of cancer, cancer diagnosis will be assessed at the index date of NVAf diagnosis and classified by cancer type into breast, prostate, colorectal, haematological, lung, and other types, and by cancer metastasis status.
- Drugs that affect either stroke or bleeding, or commonly interact with OACs, such as antihypertensive drugs, statins, antiarrhythmics, antidiabetic drugs, anticonvulsants, non-steroidal

anti-inflammatory drugs, corticosteroids, systemic azoles, HIV protease inhibitors and ciclosporin. (Appendix 2).

- The CHA2DS2-VASc stroke risk score that consists of 9 points, one for each of: congestive heart failure (CHF), hypertension (HTN), age  $\geq 75$  years (x 2 points), diabetes mellitus (DM), prior stroke or transient ischemic attack (TIA) or thromboembolism (x 2 points), vascular disease, age 65 to 74 years, and sex category. Information included in the CHA2DS2-VASc score will be identified using Read codes (Appendix 3 and 4), except for age and sex, to build the score and assess the risk of stroke for all included patients in the cohort. Further categorization of eligibility for OACs will be carried according to individual CHA2DS2-VASc scores; “not eligible for OAC” if CHA2DS2-VASc score = 0 in males, or 1 in females; and “OAC eligible” if CHA2DS2-VASc score  $\geq 1$  in males, or  $\geq 2$  in females.

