  - Bleeding risk assessment using the HAS-BLED score which consists of 9 points, one for each of: hypertension, abnormal kidney or liver function (1 point each), stroke, history of bleeding or predisposition, labile INR, elderly ( $> 65$  years), and drugs/alcohol concomitantly (1 point each). All information included in the HAS-BLED score will be identified using Read codes (Appendix 3 and 4), except for age, to build the score and assess patients’ risk for bleeding. Labile INR will not be included since it is not recorded consistently in the CPRD and because we aim is to identify the presence of prescriptions for VKA rather than checking for patient’s adherence to VKA. Bleeding tendency or predisposition will be identified through Read codes for anaemia and gastric, duodenal, and peptic ulcers (Appendix 4). Also, since alcohol consumption is not well documented in primary care, whenever possible patients will score a point for this element if there is a Read code record of heavy or problematic drinking. The bleeding risk will be categorized according to HAS-BLED score; low risk (0-1), intermediate risk (2), and high risk ( $\geq 3$ ).
  - Bleeding risk assessment using the HEMORR2HAGES score which consists of the following variables: Hepatic/renal disease (1 point each); ethanol abuse (1 point); malignancy; age  $> 75$  y (1 point); low platelets count (1); re-bleeding risk (2 points); high blood pressure (1); anaemia (1); genetic factors (1 point); falls risk (1 point); stroke (1). All these variables will be identified using Read codes (Appendix 3 and 4), except for age, to build the score and assess patients’ risk for bleeding except for genetic factors which are not accurately captured in the CPRD.
  - Combined assessment of stroke, bleeding, and mortality risk using the GARFIELD-AF model relies on the following variables: age (in years), weight, heart rate, diastolic blood pressure, ethnicity, sex, history of bleeding, heart failure, history of stroke, diabetes, smoking status, dementia, use of antiplatelet, carotid occlusive disease, chronic kidney disease (CKD) (stages III–V) and vascular disease, in which the latter is defined as history of myocardial infarction (MI) or unstable angina, aortic or peripheral artery disease. These conditions will be identified using Read codes (Appendix 3 and 4).
- All risk assessment scores will be measured at each patient’s index date.

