## **Data/statistical analysis**

1. Phase 1 - NVAF cohort: Annual and crude incidence rates of NVAF cases will be calculated and expressed as person-time at risk with 95% confidence intervals (95% CI). Incidence rates will be calculated by dividing the number of new diagnosed NVAF cases each year by the total population at risk during the same year. NVAF incidence in each calendar year of the study period (2009-2018) will be stratified by age and further standardized by age and deprivation quantiles. Status of anticoagulation therapy will be classified as either OAC prescribed or OAC not prescribed. OAC prescribed patients are those who received prescriptions for OACs during the study period. Treatment patterns for OAC users will be evaluated for OACs continuation, discontinuation or switched). OACs not prescribed will be defined as no prescription record of an OACs at any time after NVAF diagnosis, this will also include patients prescribed lone antiplatelet therapy. Proportions of patients prescribed antiplatelets will be described for both OACs prescribed and not prescribed patients. Baseline demographic, and clinical characteristics, and status of cancer diagnosis across OACs prescribed and not prescribed groups will be presented as number and percentage, mean $\pm$  (SD), or median (interquartile range), as appropriate. For both groups' eligibility for OACs will be described and categorized based on stroke risk according to CHA2DS2-VASc score. Trends in OACs initiation, switching from antiplatelet only to OACs, and from VKA to NOAC will be explored for each year and further stratified by eligibility for OACs and deprivation quantiles. To identify variables independently associated with OACs prescribing multivariate logistic regression models will be used and fitted with the covariates described in section N. Similarly, in a separate analysis for patients with NVAF and previously diagnosed cancer multivariate logistic regression models will be fitted to explore variables independently associated with OACs prescribing (i.e, cancer types and metastasis status). The level of statistical significance was set at  $P < 0.05$ .

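### Phase 1 fixes OAC eligibility at the index date but uses it to stratify yearly OAC starts and switches up to 10.5 years later, so late events in newly eligible patients fall in the wrong stratum

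*Protocol*

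**What the plan says.** Four statements in the protocol combine.

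- **Source of eligibility** (Exposures, outcomes and covariates, Phase 1, Covariates): "Further categorization of eligibility for OACs will be carried according to individual CHA2DS2-VASc scores". Men with a score of 0 and women with a score of 1 are not eligible; men with 1 or more and women with 2 or more are.
- **Timing of the score** (same section, end of the risk-score list): "All risk assessment scores will be measured at each patient’s index date". The Phase 1 covariate text names that date only once, for cancer: "cancer diagnosis will be assessed at the index date of NVAf diagnosis".
- **Window for treatment** (Phase 1, Outcomes): "OAC prescription will be defined as the presence of any OACs prescription during the study period". No limit after diagnosis is set. The Study design section says the cohort will "identify incident cases of NVAf between January 1st, 2009 and 30th of June 2019".
- **Use in the analysis** (Data/statistical analysis, Phase 1): the treatment results "will be explored for each year and further stratified by eligibility for OACs and deprivation quantiles". The events split in this way are OAC starts and two kinds of switch, from antiplatelet alone to an OAC and from a VKA to a NOAC.

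Nothing in the Phase 1 text re-measures the score at a later year, at the first prescription or at a switch. Scores are taken again only in Phase 3, at the index haemorrhage.

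**The concern.** The score has an item that changes with time alone. The list includes "vascular disease, age 65 to 74 years, and sex category", so a man with score 0, or a woman whose only point is for sex, becomes eligible on turning 65 with no other change. New hypertension, diabetes, heart failure, vascular disease or stroke has the same effect. Age and history items accumulate, so patients move from 'not eligible' to 'eligible' and not back.

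Take a man aged 60 with score 0 at diagnosis in 2009. He scores 1 from 2014. If he starts an OAC then, the start is tabulated as treatment of a patient who was not eligible. If he is not treated, he is absent from the eligible-but-untreated group whose under-prescribing the study sets out to describe. Because the fraction of patients affected rises with time since diagnosis, the misclassification could itself look like a calendar trend in OAC use among the 'not eligible'.

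**Working it through.** The protocol states no figure on this point, so there is none to reproduce. The check has two parts: whether the text leads to the problem, and how large it could be.

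**Text.** Could the index date mean something that avoids the problem? The Phase 2 analysis text does refer to an index date of OAC initiation. In Phase 1 that date cannot classify the whole cohort, because never-treated patients do not have one. Diagnosis is therefore the only workable Phase 1 reading, although the protocol does not define it formally for the scores.

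**Inputs from the protocol.** The window runs from 1 January 2009 to 30 June 2019, so F = 10.49 years. One point is gained at age 65, and that point alone is enough for eligibility.

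**Assumptions, not from the protocol.** Diagnosis dates are uniform over the window. Ages of 'not eligible' patients at diagnosis are uniform over the W years below 65. Follow-up runs to 30 June 2019 with no death or de-registration.

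**Formulas.** Follow-up is uniform on (0, F) and time to the 65th birthday is uniform on (0, W).

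- If W ≥ F: share reaching 65 in the window = F/(2W); share of follow-up time spent past 65 = F/(3W).
- If W < F: share reaching 65 = 1 − W/(2F); share of follow-up time = 1 − W/F + W²/(3F²).

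For ages 40-64 (W = 25): 10.49/50 = 0.21 and 10.49/75 = 0.14. For ages 55-64 (W = 10): 1 − 10/20.98 = 0.52 and 1 − 0.953 + 0.303 = 0.35.

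| Age at diagnosis | W | Reach 65 by 30 June 2019 | 'Not eligible' follow-up time actually eligible |
|---|---|---|---|
| 40-64 | 25 | 21% | 14% |
| 50-64 | 15 | 35% | 23% |
| 55-64 | 10 | 52% | 35% |
| 60-64 | 5 | 76% | 60% |

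A simulation under the same assumptions gives the same values.

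**Drift over calendar time.** Among patients diagnosed by time t (years since January 2009, t ≤ W), the share of the baseline 'not eligible' pool already past 65 is t/(2W).

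| | mid-2010 (t = 1.5) | mid-2013 (4.5) | mid-2016 (7.5) | mid-2018 (9.5) |
|---|---|---|---|---|
| Ages 55-64 | 7.5% | 22.5% | 37.5% | 47.5% |
| Ages 40-64 | 3% | 9% | 15% | 19% |

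**New comorbidity.** Adding an assumed 2% to 8% per year onset of a new risk factor raises the misplaced follow-up time to 19-32% (ages 40-64) and 38-46% (ages 55-64).

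These are shares of patients and of follow-up time. They are not estimates of bias in the initiation or switching rates, which would also need treatment rates that the protocol does not give.

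**The case against.** Following a diagnosis cohort by its baseline risk category is a coherent description, and index-date scores are right for the baseline tables and for the predictor model. The analysis text does not say whether a year is the year of the event or the year of diagnosis, and it states no denominator; a statistical analysis plan may settle both. If initiation is tabulated by diagnosis year, the index-date category suits it. Starts soon after diagnosis are barely affected on either reading. All of this stands, and it limits the point.

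It does not remove the point. The timing of the score is a stated rule, not a detail left open. The same paragraph of the analysis section works in calendar years. Switches necessarily follow earlier treatment, so they can come years after diagnosis.

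Three stronger readings might be inferred, and the documents do not support them.

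- *That the eligibility-stratified trend is the main under-prescribing result.* Specific aims 2 and 3 name proportions treated, trends by OAC type and factors associated with not prescribing. The eligibility split is a further descriptive cut, in a phase that the protocol calls hypothesis generating.
- *That about half of 'not eligible' person-time is misplaced.* That holds for patients diagnosed in January 2009 at 55-64 and followed for 10 years without exit (mean of 5 years to age 65, and 5/10 = 50%). Diagnoses accrue until June 2019, so it is an extreme case.
- *That the tables will show a spurious rise.* The direction follows from the text, but the size is unknown. If prescribers treat promptly when patients become eligible, little untreated time is misplaced, although each such start is still put in the wrong stratum.

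**Conclusion.** The point holds in a limited form. Followed as written, the protocol places late OAC starts and switches in newly eligible patients in the 'not eligible' stratum. If denominators use the same category, it also leaves newly eligible untreated patients out of the eligible group. The misclassification runs one way and increases with time since diagnosis.

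From age alone, about 14% to 35% of 'not eligible' follow-up time is misplaced for assumed age ranges of 40-64 and 55-64. A narrower range just below 65 gives more. Death and de-registration lower these values and new comorbidity raises them. Patients aged 65 or over at diagnosis are eligible from the start and unaffected. The effect on the whole cohort therefore depends on the number and ages of younger low-score patients, which the protocol does not give.

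The change is worth making because it concerns a named Phase 1 analysis and is cheap. It does not touch the Phase 2 comparison, the Phase 1 predictor model or the baseline description.

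**What to change.** - State that the Phase 1 index date for the risk scores is the date of NVAF diagnosis. Keep index-date scores for the baseline tables, the predictor model and prescribing at diagnosis.
- For the calendar-year initiation and switching trends, re-derive CHA2DS2-VASc eligibility at the start of each calendar year from age and codes recorded up to that date. Use the index-date score in the calendar year of diagnosis. Apply the same category to events and denominators. A patient who becomes eligible mid-year is then misplaced for less than a year.
- Say in the analysis section that year means calendar year of the event, and name the denominator.
- Label any table kept on baseline scores 'eligibility at diagnosis'.

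The eligibility cut-offs stay as they are. The cost is programming and a more complex annual table. The age and comorbidity codes are already needed for the baseline score, and Phase 3 already plans to score patients again at a later date.

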## 2. Phase 2 - Comparative study

**Exposures:** In this cohort, prescriptions for OAC will determine patient’s exposure status. NVAf patients identified from phase one and who have received a continuous prescription of either VKAs or NOACs within one year of NVAf diagnosis will be in the OACs “exposed group”. While “OACs unexposed” patients are individuals in phase one who haven’t received a prescription for anticoagulation therapy and remained OACs free for  $\geq 1$  year from NVAf diagnosis.

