### **Definition of the study population**

Patients will be identified from CPRD, both GOLD and Aurum databases will be used as the primary care data source

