## Selection of comparison groups/controls

For the second phase of this study, we aim to compare the clinical outcomes of patients with NVAf prescribed OACs and who were not prescribed OACs. This will be done by including incident cases of NVAf identified from phase one cohort from 2009 to 2019 and further divide them into two groups; cases are patients treated with OACs within one year of NVAf diagnosis and controls are those who did not receive OACs for  $\geq 1$  year after NVAf diagnosis. Many confounders will be controlled for when evaluating the effect of treatment (OACs) on the clinical outcomes of interest (i.e. stroke, bleeding, or all-cause mortality). Potential confounders are likely to include patient age, sex, and presence of hypertension, diabetes, coronary artery disease, heart failure, kidney disease, liver disease, peripheral artery disease, fall risk, history of stroke or bleeding, malignancy, anaemia, alcohol abuse, antiplatelet use or non-steroidal anti-inflammatory drugs. At first, we aim to perform propensity score matching method using a multivariable logistic regression model that contains the confounders mentioned above to estimate patient's probability to receive OACs. Matching will operate by taking each case and finds the closest propensity score match among controls, within a predetermined caliper bandwidth. However, in case if the matching method failed to achieve balance among the two patient groups or caused substantial exclusion of individuals from the main cohort, then we will consider overlap propensity score weighting. By applying overlap propensity score weighting each patient's will be weight by the probability of that patient being assigned to the opposite treatment group.

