2. Phase 2 – Comparative study: For comparison of demographic variables and comorbidities among OACs treated and not treated individuals, independent sample t tests will be used for numeric variables, while Chi squared  $\chi^2$  tests or Fisher exact tests will be used for categorical variables. To control for imbalances in patient characteristics between cohorts, we will calculate an exposure-specific propensity score as the predicted probability of receiving OACs conditional upon individuals baseline covariate (as described in section M) using logistic regression models. Then we will consider applying propensity score matching methods to match each OACs unexposed controls to up to 5 NVAF OACs exposed cases using a calliper of 0.2 standard deviation (SD) of the propensity score logit. After matching, Cox regression will be used to compute hazard ratios (HRs) of the outcomes of interest, comparing exposure to OACs versus no OACs. Initially crude HRs will be obtained, then stratified by type of OACs (i.e., VKAs and NOACs) and adjusted for age, and other important covariates described in section N. In this phase immortal time bias would occur due to the definition of exposure, where in the time from AF diagnosis till receipt of OACs those in the “OACs prescribed group” cannot have the outcome by design, otherwise they would have been classified as non OAC users. To avoid the problem of immortal time bias, we will consider using time-varying exposures, where in a survival analysis, the time period previous to the index date of OACs initiation is reclassified as nonuser for those in the “OACs prescribed group”.

3. Phase 3 – Major bleeding events cohort: At first, we will use descriptive statistics to present the overall characteristics of this cohort who have experienced major bleeding events while taking OACs. After that patients will be divided to 2 groups one for the patients who resumed anticoagulation after the index major bleeding event and the other for the group who remained OACs free and will compare the patient characteristics between the two groups using Chi squared  $\chi^2$  tests, Fisher's exact tests, and analysis of variance, as appropriate. Survival (time-to-event) models will be constructed to compare the time between the indexed major bleeding to the earliest event of stroke, bleeding, or all-cause mortality considering if patients were restarted on OACs or not. In Cox models we will control for age, time to OACs resumption, CHA2DS2-VASc

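### The Phase 2 definition of the OAC-exposed group does not require treatment to start after NVAF diagnosis, whereas the immortal-time remedy presumes that it does; patients already on an OAC can enter

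*Protocol*

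**What the plan says.** The exposed group is defined twice. Under Selection of comparison groups/controls, "cases are patients treated with OACs within one year of NVAf diagnosis". Under Exposures, outcomes and covariates, Phase 2, exposed patients are those "who have received a continuous prescription of either VKAs or NOACs within one year of NVAf diagnosis". Neither definition says that the prescription must be the first, or that the patient was free of OACs beforehand.

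Phase 1, which supplies the patients, is wider for the treated and looks only forward for the untreated: "OAC prescription will be defined as the presence of any OACs prescription during the study period", while "OACs not prescribed will be defined as no prescription record of an OACs at any time after NVAf diagnosis".

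The control group is also described twice. The selection section asks only that no OAC was received for at least one year after diagnosis. The Phase 2 Exposures paragraph describes people who have not "received a prescription for anticoagulation therapy and remained OACs free" for at least one year from diagnosis; the negative applies to the prescription.

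Under Data/statistical analysis, item 2, the protocol recognises immortal time bias between AF diagnosis and receipt of an OAC. It answers with "we will consider using time-varying exposures", under which, for the OAC group, "the time period previous to the index date of OACs initiation is reclassified as nonuser".

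The section Definition of the study population reads, in full, "Patients will be identified from CPRD, both GOLD and Aurum databases will be used as the primary care data source". The text shown contains no washout. Prior OAC use is not among the propensity-score confounders listed, although that list is introduced as likely rather than final.

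**The concern.** Aim 4 asks what prescribing an OAC, compared with not prescribing one, does to stroke, bleeding and death in patients with newly diagnosed NVAF. That comparison needs treated patients whose treatment begins at or after the point where follow-up can begin. The protocol requires the NVAF to be incident but does not require the OAC use to be.

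A patient already anticoagulated when NVAF is first coded differs from a starter in two ways. First, that patient has already come through the early period of treatment without dying or stopping. Second, bleeding history, anaemia, antiplatelet use and the risk scores are taken at the index date, when treatment may already have altered them. The propensity model would then adjust for possible consequences of exposure.

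The time-varying analysis does not help here. It moves time between diagnosis and initiation into the non-user category, and an established user has no such time. Phase 3 is drawn from exposed patients who bleed, so any mixture carries forward.

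**Working it through.** **Step 1: the passages side by side, for a patient on an OAC before the first NVAF code who continues afterwards**

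- *Selection of comparison groups:* treated within one year of diagnosis. The patient qualifies.
- *Phase 2 Exposures:* continuous prescription within one year. The patient qualifies.
- *Phase 1 Outcomes:* any prescription in the study period. The patient is labelled as prescribed. Continuous exposure is dated from the first prescription, which here precedes diagnosis.
- *Data/statistical analysis:* reclassify time from diagnosis to initiation. That interval is empty, and the step is only to be considered.

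The entry rules therefore admit the patient, while the analysis text describes a patient of another kind.

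**Step 2: a patient whose OAC stopped before diagnosis and who has none for a year afterwards**

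- *Selection of comparison groups:* qualifies as a control, because only the year after diagnosis is tested.
- *Phase 2 Exposures:* can be read as excluding the patient, since the no-prescription clause has no start date.
- *Phase 1 Outcomes:* prescribed under one sentence, if the old prescription fell in the study period; not prescribed under the other, which looks only after diagnosis.

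The texts do not agree.

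**Step 3: possible size for bleeding**

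The protocol gives no figure on this point to reproduce. It states neither the share of established users nor how bleeding risk changes with time on treatment. Every input below is an assumption:

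- *f*: share of established users in the exposed group, 0.05 to 0.30
- *k*: bleeding rate relative to non-users in the first 90 days (about 0.25 year) of treatment, 2 to 4
- *l*: the same after 90 days, 1.0 to 1.3; established users carry *l* throughout
- rare events, one year of treated follow-up, hazard ratio approximated by the average rate ratio

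Starters only: HR = 0.25k + 0.75l

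Mixed group: HR = (1 − f)(0.25k + 0.75l) + f·l

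Relative fall = 0.25·f·(k − l) / (0.25k + 0.75l)

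| k | l | f | Starters | Mixed | Fall |
|---|---|---|---|---|---|
| 3 | 1.0 | 0.10 | 1.50 | 1.45 | 3.3% |
| 3 | 1.0 | 0.20 | 1.50 | 1.40 | 6.7% |
| 3 | 1.0 | 0.30 | 1.50 | 1.35 | 10.0% |
| 4 | 1.0 | 0.30 | 1.75 | 1.525 | 12.9% (largest) |
| 2 | 1.3 | 0.05 | 1.475 | 1.466 | 0.6% (smallest) |

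**Step 4: longer follow-up**

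Outcomes are counted over the course of follow-up, with no one-year limit. Over three years the first 90 days are 0.25/3 = 0.083 of the time. With k = 3, l = 1.0 and f = 0.20, starters have 0.083 × 3 + 0.917 × 1 = 1.167. The mixed group has 0.8 × 1.167 + 0.2 × 1 = 1.133. The fall is 2.9%, against 6.7% at one year.

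**The case against.** The strongest reply is that the protocol is silent on established users and does not expressly admit them. Study design speaks of incident cases and of prescribing that comes afterwards. The immortal-time paragraph describes time from diagnosis to receipt of an OAC and an initiation date. Continuous exposure is dated from the first prescription. The study-population section is a single sentence that may have been cut short, so an exclusion could once have stood there, and a look-back window might be set in an analysis plan that is not at hand.

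Part of this stands. The authors probably had starters in mind. But a presumption in the analysis text is not an entry condition, and the two operative definitions of the exposed group, which appear complete, do not contain one.

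A reader might go further and infer that established users enter as exposed from day 0, and that the bleeding and mortality hazard ratios are therefore biased in favour of OACs. The documents do not support that:

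- No passage fixes when exposed time starts for such a patient.
- Some apparent established users would be late-coded AF patients who are in effect starters.
- Others would be anticoagulated for another reason and may have a higher underlying risk of bleeding or death, which pushes the hazard ratio the other way.
- No effect on mortality, or on the primary composite of thromboembolism and major bleeding, can be derived.

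A reader might also infer that former users are plainly admitted as controls. The selection section allows it, but the Phase 2 wording, with its unlimited first clause and its reference to remaining OAC-free, points the other way. This is a conflict in wording and not a clear rule.

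**Conclusion.** The point holds as a gap and an inconsistency. As written, patients already on an OAC at first NVAF coding can enter the Phase 2 exposed group. The proposed time-varying rule does nothing for them, and their covariates are measured after treatment began. The two control definitions need to be reconciled on former users.

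Dilution of the bleeding hazard ratio is conditional: it requires that such patients are present, that bleeding risk is highest soon after starting, and that their underlying risk is otherwise comparable. On the wholly assumed inputs above, the one-year hazard ratio falls by about 0.6-13%, and by less with longer follow-up. The effect may therefore be modest. The direction for mortality and for the composite is not established.

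It should still be settled before analysis, because cohort entry and exposure are defined in this protocol, Phase 2 is declared hypothesis testing, and the correction uses data already held.

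**What to change.** Put the same rule in Selection of comparison groups/controls and in the Phase 2 Exposures paragraph:

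1. For both groups, require no OAC prescription in a stated look-back period (for example 12 months) before the first NVAF code. Allow a short window (for example 30-60 days) just before that code for late coding of AF.
2. Date exposure from the first qualifying OAC prescription, in line with the initiation date in the analysis section. Where that prescription falls inside the coding allowance, start follow-up at the NVAF code, so that the days before it are not counted as time at risk.
3. Use one wording for controls, stating whether OAC use before the look-back period disqualifies a patient.
4. Report the number of established users excluded, and add them back in a sensitivity analysis.

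The cost is a short eligibility text, and enough registered history before diagnosis to verify the look-back. Phase 2 would have somewhat fewer exposed patients, where the protocol calculates a need for 970 and expects many times the required total. That margin was calculated for stroke in Phase 2 only. Phase 3 takes its patients from the exposed group and would also be somewhat smaller, so its expected number should be checked.
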